### Relevant concomitant care permitted or prohibited during the trial

Participants could maintain their regular course of care and medication schedule except for other Vitamin D supplements during the study, and physicians are advised to manage participants in accordance with standard practice while taking the previously mentioned precautions into account.

### Provisions for post‑trial care

Not applicable, since ancillary and post-trial care is provided within the standard care.

### Outcomes and outcome assessments

The primary outcomes will be muscle strength using quadriceps and hamstring muscle assessments, and the secondary outcomes will be the post-intervention change in muscle strength function from baseline using 5-time chair stand test, sarcopenia assessment by Dual Energy X-ray Absorptiometry (DXA), handgrip strength and 6-meter gait speed test, six questionnaires: Western Ontario and McMaster Universities Osteoarthritis Index (WOMAC), Knee Injury and Osteoarthritis Outcome Score (KOOS), Short-Form 36 (SF-36), International Physical Activity Questionnaire (IPAQ), Nutritional Intake and Sunlight Exposure questionnaire (Questionnaires can be seen in S5 File), and biochemical assays including serum Vitamin D level and myokines. Blood samples will be taken under non-fasting conditions. The serum obtained will be immediately stored at -80°C until analysis.

Outcome assessments of the patients will be performed at baseline (0 month), 3 months and 6months after the commencement of vitamin D supplement, and 6-month after the interventional period.

#### Knee muscle strength

The primary outcome will be obtained by measurement of knee muscle strength using a hand-held dynamometer (Hoggan Scientific, Salt Lake City, UT, USA) to assess maximal voluntary quadriceps and hamstring muscle strength. Each participant will be placed on an examination table with their feet elevated and their knees bent at a 60°. The maximal voluntary quadriceps muscle strength on the anterior aspect of the distal tibia (see Fig 3) and the maximal voluntary isometric hamstring muscle strength will be measured using the hand-held dynamometer placed on the posterior portion of the lower leg (see Fig 4). For stability, participants will hold onto the examination table with their hands. They will then be told to flex or extend their knee "as hard as possible" into the hand-held dynamometer. For five seconds, participants will keep applying force to the hand-held dynamometer, and the maximum force they can muster during the experiment will be noted. All tests will involve maximal voluntary isometric contractions. Both limbs will be assessed to record. Two testing trials will be completed. The maximum knee extensor and flexor strength were calculated to obtain an overall muscle strength value (kgf) divided by the patient’s body mass.

**Fig 3 pone.0309610.g003:**
[figure not shown]
Quadriceps muscle strength test.

**Fig 4 pone.0309610.g004:**
[figure not shown]
Hamstring muscle strength test.

#### 5-time chair stand test

This test is a reliable and validated tool for the measurement of lower limb strength [28]. Patients will sit on a chair with their feet shoulder-width apart and their arms resting on their shoulders. They will complete five reputations across two trials and one or two repeats of the test to get comfortable with it. We’ll keep track of time in seconds.

#### Dual energy X-ray absorptiometry (DXA)

For a single, 20-minute session of muscle mass evaluation, the radiation dose is less than 25μSv, falling within the acceptable limit. Two copies of the patient’s body composition including total fat percentage, body mass index, and—most importantly for this study—lean appendicular muscle mass will be printed following each DXA scan.

#### Handgrip strength

The maximal handgrip strength (kg) will be evaluated for knee OA patients using the handgrip dynamometer. After three iterations of the test, the dominant hand’s average will be determined.

#### Definition of sarcopenia

Sarcopenia was defined by following the Asian Working Group for Sarcopenia (AWGS2) algorithm [29]. A patient with low muscle mass, low muscle strength, and/or low physical performance was categorized as having sarcopenia. Low muscle mass was defined as height-adjusted muscle mass by DXA < 7.0 kg/m^2^ for men and < 5.4 kg/m^2^ for women; low muscle strength was defined as grip strength < 28 kg for men and < 18 kg for women; and low physical performance as gait speed < 1.0 m/s for both men and women.

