## Introduction

One of the most prevalent chronic degenerative disorders is osteoarthritis (OA) of the knee. Older adults who experience it become disabled, causing discomfort and stiffness. Among persons over 60, the prevalence of radiologic knee OA was 37.4%, while that of symptomatic knee OA was 12.1% [1]. With just 4300 total knee replacements conducted in 2021, the Hospital Authority (HA) had over 26,000 patients on its waiting list for knee total knee replacements (TKRs), meaning that the estimated waiting period in Hong Kong was about 89 months [2]. The number of people with end-stage knee OA who are waiting for surgery is anticipated to rise sharply as the population ages. While waiting for TKR, patients with end-stage OA can benefit from additional therapies to help them function better and maintain overall health.

Patients with end-stage knee OA frequently give up on physical activity to prevent joint stiffness and pain, which can negatively impact overall muscle health and localized knee function. As people age and become less active, their muscular mass and strength gradually decrease to an unusually low level known as "sarcopenia" [3]. Older adults with sarcopenia are more likely to have a decline in functional outcomes and a greater death rate, which puts a strain on their finances and healthcare system [4]. On the other hand, sarcopenia was found in 32.8% of patients with end-stage knee OA in a previous study on the prevalence of sarcopenia in end-stage knee OA patients. These patients likewise recovered more slowly following TKR [5]. A recent study categorized “sarcopenic knee OA” patients as a new subgroup with a higher risk of falling and associated risk factors than patients with sarcopenia or knee OA alone [6]. Strengthening exercise has been indicated to improve muscle mass, strength, and gait speed among sarcopenic patients [7]. However, the individual responses to exercise are variable [8].

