### Objectives

The study aims to investigate the effect of vitamin D supplementation on knee muscle strength, physical function, pain symptoms, and sarcopenia status in end-stage OA knee patients.

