### Statistical analysis

Data in this study will be analyzed according to the intention-to-treat principle. Only the full analysis set and per-protocol set will be used for primary outcome analysis. The last observation carried forward (LOCF) will be used to impute the missing data by replacing it with the last observed value.

Quantitative variables will be expressed as mean ± standard deviation. Normality tests will be performed to determine whether the data is normally distributed. A one-way analysis of covariance (ANCOVA) tests with Bonferroni correction and with the baseline value as a covariate was conducted at 3m,6m, and 12m to determine the group effect on each parameter. Independent T-test (two-tailed) are used for multiple testing of continuous variables. Whereas the Chi-square test will be used to compare the proportions of categorical variables and to calculate the differences in the count data. A repeated measure analysis of variance (ANOVA) will be used to analyze the trend of changes in the scores among four-time points (Baseline, 3m, 6m, 12m) to determine the group×time effects. Post hoc analysis with Bonferroni correction will be conducted to explore the differences between baseline and 3m, baseline and 6m, 6m and 12m. The statistical analysis will be performed using commercialized statistical software (SPSS, version 29.0, IBM). All statistical significance is defined as P < 0.05.

Additional analyses will include subgroup analyses to estimate treatment effects for both female and male participants, normal BMI and overweight or obese participants.

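### The sarcopenia definition does not say which criteria are mandatory, and the only test given for proportions leaves out baseline status

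*Protocol article*

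**What the plan says.** The Objectives section of the protocol article lists the targets as "knee muscle strength, physical function, pain symptoms, and sarcopenia status in end-stage OA knee patients". The section on outcomes places the sarcopenia assessment (DXA, handgrip, 6-metre gait speed) among the secondary outcomes, measured at baseline, 3, 6 and 12 months.

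The section Definition of sarcopenia states that a cited Asian Working Group algorithm is followed and then gives the rule: "A patient with low muscle mass, low muscle strength, and/or low physical performance was categorized as having sarcopenia". Sex-specific cut-offs for muscle mass and grip follow, with "low physical performance as gait speed < 1.0 m/s for both men and women". No sentence says that any one criterion must be present.

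The Introduction describes the condition differently: as people age and become less active, "their muscular mass and strength gradually decrease to an unusually low level known as" sarcopenia. It also quotes a prevalence of 32.8% in end-stage knee OA from a previous study.

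Under Statistical analysis, the method for categorical data is: "Chi-square test will be used to compare the proportions of categorical variables and to calculate the differences in the count data". The baseline covariate appears only in the ANCOVA sentence, "with the baseline value as a covariate was conducted at 3m,6m, and 12m to determine the group effect on each parameter".

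**The concern.** A binary outcome is only as well defined as its classification rule. Here the rule is one list closed by an and/or. An analyst who codes that sentence as it stands will call a patient with normal muscle mass and normal grip sarcopenic if gait is below 1.0 m/s. The Discussion describes patients waiting for knee replacement as being in severe pain with marked functional impairment, so slow walking may reflect the knee rather than the muscle. The outcome could then largely repeat the gait test, which is already reported separately. If the rule stays open until the data are in, the choice between readings could also be made with the results in view.

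The second matter is efficiency. Eligibility does not restrict sarcopenia status, so cases and non-cases are mixed at entry, and status at entry is likely to predict status later. The plan adjusts for baseline in its ANCOVA but offers no counterpart for a binary outcome.

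**Working it through.** **The plan's own figures.** No prevalence, effect or power is stated for sarcopenia status. The sample size concerns quadriceps strength only (23 per group, raised by 20%: 23 × 1.2 = 27.6, so 28) and does not bear on this point. The one related figure is the cited 32.8%.

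**Step 1: what each reading counts.** The three criteria give 2 × 2 × 2 = 8 patterns.

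| Criteria met | Any one | Mass plus either other | (Mass and strength) or gait | All three |
|---|---|---|---|---|
| none | no | no | no | no |
| gait only | yes | no | yes | no |
| strength only | yes | no | no | no |
| strength and gait | yes | no | yes | no |
| mass only | yes | no | no | no |
| mass and gait | yes | yes | yes | no |
| mass and strength | yes | yes | yes | no |
| all three | yes | yes | yes | yes |
| **Patterns counted** | **7** | **3** | **5** | **1** |

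Gait alone qualifies under the first and third readings. Neither matches a condition described as loss of mass and strength.

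**Step 2: how many patients that could move.** The component rates are assumptions, as is independence; the protocol gives neither. Take low mass 35%, low strength 30-40%, slow gait 40-60%.

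- Any one = 1 − (1 − mass)(1 − strength)(1 − gait). Low end: 1 − 0.65 × 0.70 × 0.60 = 0.727. High end: 1 − 0.65 × 0.60 × 0.40 = 0.844.
- Mass plus either = mass × [1 − (1 − strength)(1 − gait)]. Low end: 0.35 × (1 − 0.70 × 0.60) = 0.203. High end: 0.35 × (1 − 0.60 × 0.40) = 0.266.

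Of 56 patients, that is about 41-47 against 11-15.

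With wider assumed ranges (mass 20-45%, strength 30-50%, gait 30-70%, still independent), the results are 61-92% for any one, 10-38% for mass plus either and 2-16% for all three. The first two ranges do not overlap.

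Independence is not essential to the direction. Any one is never below the commonest single criterion, and mass plus either is never above the rate of low mass. With the first set of rates, that means at least 40% against at most 35%.

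**Step 3: what the unadjusted test costs.** Assumed transitions:

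- baseline prevalence 32.8%;
- control: 90% of cases persist and 5% of non-cases become cases;
- vitamin D: 40% persist and 2% become cases.

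Follow-up rates are then 0.328 × 0.90 + 0.672 × 0.05 = 32.9% on control and 0.328 × 0.40 + 0.672 × 0.02 = 14.5% on vitamin D. Rejection rates over 4,000 simulated trials:

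| | Chi-square | Mantel-Haenszel stratified by baseline status |
|---|---|---|
| Power, 28 per arm | 38% | 62% |
| Power, 23 per arm | 32% | 52% |
| No effect, 28 per arm | 5.4% | 3.3% |
| No effect, 23 per arm | 4.6% | 2.9% |

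The chi-square test holds its error rate. The stratified test gains power without exceeding 5%.

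**The case against.** The strongest reply is that the definition names a published algorithm before restating it. The and/or joins only the last two items, so the authors may mean low mass together with low strength and/or low performance. That stands: the sentence is ambiguous, and a reader who infers that the protocol plainly adopts an any-one rule goes further than the text. It does not remove the point. The algorithm's content is not reproduced in the article, and the restated sentence is what would be coded.

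A reader might also infer that the any-one rule cannot agree with the cited 32.8%, or that most trial patients would be labelled sarcopenic. The document supports neither. Three independent criteria at 12.4% each give 1 − 0.876³ = 32.8%, and the definition behind the cited figure is not shown. Agreement would need no single criterion to exceed 32.8%, which may be doubtful for gait in these patients, but that is a judgement. Nor does the Introduction's mention of a new subgroup help, because it comes from a different study from the 32.8%.

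On the test, a reader might infer that chi-square lets chance baseline imbalance pass as a treatment effect. It does not. An imbalance of 3 patients in 28 is 10.7 percentage points, while one standard error of the difference at 32.8% is √(2 × 0.328 × 0.672 / 28) = 12.5 points. The test already allows for variation of that size. It is also fair that chi-square is never assigned to sarcopenia by name. It is inferred as the only method given for proportions, and a fuller analysis plan may specify something else.

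**Conclusion.** The point holds as a gap in definition plus an efficiency suggestion. The definition carries most of the weight: a named objective rests on a sentence that admits readings counting 7, 5, 3 or 1 of 8 patterns. The literal one does not fit the protocol's own description of the condition. The pattern counts need no assumption. The split of about 73-84% against 20-27% depends on assumed component rates and independence, and shows only that the choice of reading matters.

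The unadjusted chi-square is valid under randomisation; what is lost is precision. The gain from 38% to 62% power rests on a large assumed effect and should be read as an illustration. The continuous components (lean mass, grip, gait speed) fall under the baseline-adjusted ANCOVA already planned for each parameter, so the muscle information does not hang on the binary label alone. This is a secondary outcome; the primary analysis and sample size are not touched.

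**What to change.** 1. In Definition of sarcopenia, state which criteria are mandatory and which are alternatives, and reconcile the sentence with the cited algorithm. The Introduction's description suggests that low muscle mass is required, but this must be checked against that source. Settle it before unblinding; the protocol breaks the code only after database lock.
2. In Statistical analysis, name the comparison for sarcopenia status: arms compared at 6 months, adjusted for baseline status, by logistic regression with a Firth penalty, or by a stratified exact or Mantel-Haenszel test if cells are sparse.
3. Leave the planned ANCOVA of the components as it is.

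The cost is one sentence in each section. No new data, visits or patients are needed.

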#### Western ontario and mcmaster universities osteoarthritis index (WOMAC)

Self-reported pain, stiffness, and physical function will be measured using WOMAC, which has a total score of 96. A higher score denotes an individual with greater disability [30].

#### Knee injury and osteoarthritis outcome score (KOOS)

Pain, other symptoms, function in daily living (ADL), function in sport and recreation (Sport/Rec), and knee-related quality of life (QOL) are the five separately subscales used in KOOS, which was designed to assess symptoms and function in patients with knee injury and osteoarthritis. Lower scores mean worse condition of the patients [31].

#### Short-form 36 (SF-36)

The validated and dependable Short-Form 36 questionnaires will be used to measure health-related quality of life [30]. The questionnaires consist of 36 items that measure a patient’s functional health and well-being from the perspective of the patient. The patients’ physical and mental health are summarized by this trustworthy and established assessment.

#### International physical activity questionnaire (IPAQ)

We will also evaluate the level of physical activity and inactivity for each patient. Three categories—Category 1 Inactivity, Category 2 Minimally Active, and Category 3 HEPA Active—will be calculated by this questionnaire based on the weekly activity report from patients [32].

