### Sample size calculation

Based on our power calculation, we aim to recruit 28 patients for both groups, with a total of 56 participants. Quadriceps muscle strength measured by the handheld dynamometer will be the primary outcome for sample size estimation. The effect size of the isometric quadriceps muscle strength has been determined as 0.34 in patients with knee OA [36]. A repeated-measures one-way analysis of variance (ANOVA) will be used to compare knee muscle strength, muscle mass, physical functional test, biomarkers, and questionnaire score for four timepoints (before the vitamin D supplementation (Baseline), at 3months, 6 months, and 12 months after the commencement of vitamin D supplementation). When the sample size is 23 per group with 4 repeated measurements, will have 80% of the power to detect at the 0.05 significance level. An additional 20% will be added to account for possible attrition. Thus, our sample size of 28 participants per group (total *n* = 56) will be sufficient to achieve our objective. The sample size was calculated using G*Power 3.0 software.

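### IPAQ is derived only as three ordered categories, which the plan's general rule for categorical data would compare without regard to their order or to baseline; information already collected is lost, by an amount that depends on assumptions

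*Protocol article*

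**What the plan says.** - *Outcomes and outcome assessments* places IPAQ in the list of questionnaires that are secondary outcomes ("International Physical Activity Questionnaire (IPAQ), Nutritional Intake and Sunlight Exposure questionnaire"), measured at baseline, 3 months, 6 months and 6 months after the intervention ends.
- *International physical activity questionnaire (IPAQ)* gives the form of the result: "Three categories—Category 1 Inactivity, Category 2 Minimally Active, and Category 3 HEPA Active—will be calculated by this questionnaire". The input is what patients report of their activity over a week, and a source is cited. No weekly amount is derived.
- *Statistical analysis* has one rule for categorical data: "the Chi-square test will be used to compare the proportions of categorical variables". It names no ordinal test and does not mention IPAQ.
- The same section plans a one-way ANCOVA "with the baseline value as a covariate was conducted at 3m,6m, and 12m to determine the group effect on each parameter", and the threshold is "All statistical significance is defined as P < 0.05".
- *Sample size calculation* describes a repeated-measures ANOVA for a list of outcomes that includes "biomarkers, and questionnaire score for four timepoints".

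**The concern.** Three steps can each discard information. Turning a weekly report into three levels removes every difference in activity within a level. A 2-df chi-square test then treats inactive, minimally active and HEPA active as unordered labels. It also has no place for the baseline level, although IPAQ is measured at baseline and quantitative outcomes get a baseline covariate.

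The Introduction says that these patients tend to give up physical activity because of pain and stiffness, so activity belongs to the trial's rationale. With 28 per arm there is little power to spare. A real change could be reported as no difference because patients moved within a category, or because a consistent upward shift was tested as if it could lie in any direction.

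**Working it through.** **1. The plan's own figure.** The article gives no power for IPAQ. Its only effect size is 0.34, for isometric quadriceps strength. Reproducing the sample size shows how to read it. For a repeated-measures ANOVA, between-group test, with f = 0.34, m = 4 measurements and an assumed correlation of 0.5:

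λ = f² × N × m / (1 + (m − 1)ρ) = 0.1156 × 46 × 4 / 2.5 = 8.51, with F on 1 and 44 df. Power is 0.814.

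N = 46 (23 per group) is the smallest total that reaches 80%, and 23 × 1.2 = 27.6, rounded to 28. The 0.34 therefore behaves as Cohen's f, which for two equal groups is d = 2f = 0.68 SD. Shifts of 0.34 SD (taken at face value) and 0.68 SD (read as f) are used below as a range. Neither is a figure for physical activity.

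**2. Assumptions not in the article.** Latent activity is normal in each arm, shifted by d in the vitamin D arm. The three categories are cuts of that one amount. Control-arm splits are 33/33/33, 25/50/25, 50/35/15 and 60/30/10. Baseline correlation is 0.5. Two-sided alpha is 0.05. There are 23 (evaluable) or 28 (randomised) per arm and 20,000 simulated trials per scenario.

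**3. Tests compared.** Pearson chi-square Σ(O − E)²/E on the 2×3 table (2 df); Wilcoxon on the three ordered categories; Wilcoxon on the uncut amount; ANCOVA on the uncut amount with baseline; and an untransformed t-test when the amount is log-normal. Under no effect, rejection is about 5% for the chi-square, ordered-category, rank and rank-ANCOVA tests. Power in %, with ranges over the four splits:

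| n per arm | Shift (SD) | Chi-square, 3 categories | Ordered test, 3 categories | Rank test, uncut | ANCOVA, uncut | Raw t-test, log-normal |
|---|---|---|---|---|---|---|
| 23 | 0.34 | 12.3–13.8 | 16.7–17.4 | 19.7 | 24.8 | 14.1 |
| 23 | 0.50 | 22.5–24.5 | 30.0–31.5 | 36.3 | 46.7 | 26.1 |
| 23 | 0.68 | 40.2–42.3 | 50.8–52.0 | 59.5 | 73.6 | 44.1 |
| 28 | 0.34 | 15.1–16.2 | 19.0–20.4 | 23.2 | 30.0 | 16.8 |
| 28 | 0.50 | 27.7–29.6 | 35.9–37.4 | 43.2 | 56.0 | 31.4 |
| 28 | 0.68 | 48.3–49.9 | 58.6–60.2 | 67.8 | 81.3 | 51.7 |

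**4. Loss of chi-square against the uncut amount.**
- At 0.34 SD: from 19.7 − 13.8 = 5.9 to 23.2 − 15.1 = 8.1 points. Adding the splits 20/60/20 and 40/40/20 gives 6 to 9.
- At 0.68 SD: from 59.5 − 42.3 = 17.2 to 67.8 − 48.3 = 19.5 points. The added splits give 17 to 20 against the rank test, and about 22 against a t-test if activity really is normal (20/60/20, 28 per arm).
- At 0.2 SD: only about 1 to 4 points.
- With a sparse top category (70/25/5) at 0.68 SD and 28 per arm: 23 points against the rank test and 26 against the t-test.

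**5. Where the loss arises (28 per arm, 33/33/33).** At 0.68 SD, ignoring order costs 58.6 − 48.7 = 9.9 points and the cut costs 67.8 − 58.6 = 9.2. At 0.34 SD the parts are 20.4 − 16.2 = 4.2 and 23.2 − 20.4 = 2.8. So about half comes from each step.

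**6. Baseline.** Against the ANCOVA the loss runs from 24.8 − 13.8 = 11 to 73.6 − 40.2 = 33 points. A rank-based ANCOVA with 28 per arm reaches about 27–29% at 0.34 SD and 78–79% at 0.68 SD.

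**7. Skew.** An untransformed t-test on log-normal activity gains only about 0 to 4 points over chi-square (for example 44.1 − 40.2 = 3.9).

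**The case against.** **The test is inferred.** The chi-square sentence is generic, and sarcopenia status alone would give it a use. The sample-size section sends questionnaire scores to a repeated-measures ANOVA, and the ANCOVA sentence covers every parameter. A reader might conclude that the plan prescribes chi-square for IPAQ; it does not say so. This stands. However, the only IPAQ result derived is a category, so an ANOVA or ANCOVA would run on codes 1 to 3. That would use order, and ANCOVA would also use the baseline code, but the loss from the cut would remain.

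**The categories have a basis.** They are presented as the questionnaire's own, with a cited source. A reader might infer an arbitrary or data-driven cut; the article does not support that. The criticism is of using the categories as the only analysed form.

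**The loss is not a property of the trial.** The 0.34 belongs to quadriceps strength, the splits and correlation are assumed, and the article does not describe the categories as cuts of a single total. This stands, so no single figure should be quoted.

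**The outcome is peripheral.** Activity is absent from the objective and from the Abstract's secondary outcomes, and function is also measured by WOMAC, KOOS, SF-36, gait speed and chair stand. At 0.34 SD even the better analysis probably misses the effect. This limits the weight of the point.

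**An unseen analysis plan may add a weekly total.** It may. The point concerns only the form that the article itself states.

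**Conclusion.** The point holds in a limited form. The article derives IPAQ only as three ordered categories, and its one rule for categorical data would, if applied, ignore both order and baseline. Under the stated assumptions, chi-square gives up about 1 to 4 points of power at 0.2 SD, 6 to 9 at 0.34 SD and 17 to 22 at 0.68 SD against the uncut amount, and more against a baseline-adjusted analysis. The top of the last range applies to a t-test on normal activity; against a rank test it is 17 to 20.

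A reader might take the larger losses as what this trial will suffer. The documents give no effect size, spread or category split for activity, so that cannot be concluded. Nor does anything here touch the muscle-strength result. It is a low-priority improvement to one secondary outcome.

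**What to change.** In the IPAQ section, define the analysed outcome as total weekly activity computed from the same questionnaire answers. In *Statistical analysis*, name its test: a rank-based or log-transformed ANCOVA between arms at 3, 6 and 12 months, with baseline activity as covariate. Keep the three categories as description. If they are to be compared, use a proportional-odds model with baseline category in place of chi-square.

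The cost is analysis wording only: no new data, visits or patients. Recruitment was still ongoing at the time of the article, and codes are broken only after database lock, so the change can be fixed in advance of unblinding. The one drawback is that weekly activity is likely to be skewed, which is why ranks or a transformation must be specified; an untransformed t-test would gain little.
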